**JHM IRB - eForm A – Protocol**

- **Use the section headings to write the JHM IRB eForm A, inserting the appropriate material in each. If a section is not applicable, leave heading in and insert N/A.**
- **When submitting JHM IRB eForm A (new or revised), enter the date submitted to the field at the top of JHM IRB eForm A.**

***************************************************************************************************

**Personalized Treatment Planning for Radioiodine Therapy of Thyroid Disease**

**Protocol Version 1.0, dated December 17, 2017**

1. **Abstract**

The Collar Therapy Indicator (CoTI), a device placed in cloth collar around the neck resembling a turtle neck sweater collar with a connecting wire and recording box (Fig. 1), has been shown in a single small previously published experience to provide data regarding radioiodine exposure that correlates with conventional methods of measuring I-123 and I-131 uptakes after diagnostic dose administration and/or therapy for thyroid disorders . We hypothesize that the device’s continuous measurement capability will permit more accurate estimates of radiation exposure to thyroid tissue than conventionally employed methods assessing fractional uptake at one or a few time points. It may also provide information about the extent of variability in the absorbed radiation dose among patients with thyroid cancer and hyperthyroidism. By providing more complete information about individual patient’s exposures, it will facilitate more accurate estimation of the administered I-131 dose requirements for both control of hyperthyroidism and thyroid remnant ablation while reducing the need for repeated visits to the clinic for dosimetry measurements. The aims of our project include the following: (1) Compare quantitative imaging-derived thyroid time activity curve to that obtained using the CoTI and to determine the extent to which there is variability in radiation dose predicted using conventional methods to that predicted from measurement of the full Time-Activity Curve (TAC); (2) Evaluate the uptake and clearance kinetics across the 5 patients in each category as proof of principle for a potential larger trial to investigate use of this device in optimizing the administered doses of radioactive iodine to achieve therapeutic goals while minimizing risks of comorbidities, such a post-radioiodine hypothyroidism in patients with Graves disease. (3) Evaluate patient experience, convenience, and discomfort in using the CoTI device with a survey instrument.

1. **Objectives** (include all primary and secondary objectives)

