**Data collection, follow up;**

Baseline data will include age, gender, BMI; duration of autoimmune thyroid disease and/or differentiated thyroid cancer, History/details of thyroid cancer (stage, FNA findings, final tumor histopathology, presence of lymph node metastasis thyroglobulin levels- baseline and stimulated, preoperative ultrasound findings, extent of surgery); presence of co-morbidities, details of autoimmune thyroid disease (prior anti-thyroid regimen including duration of discontinuation, thyroid function tests (free thyroxine, triiodothyronine, TSH), and thyroid stimulating immunoglobulins ), duration and history of levothyroxine therapy (in cases with thyroid cancer), results of neck and thyroid ultrasound, measured neck circumference prior to application of device, quality of life scores as measured by a questionnaire. Imaging data would be acquired as outlined above.

1. Study duration and number of study visits required of research participants.

**The study duration for an individual participant is 10 days and for the overall study would be 2 years but hopefully will be completed in 6 months depending on the ease of recruitement of patients.**

1. Blinding, including justification for blinding or not blinding the trial, if applicable.

**Since it is a device placed around the neck, it cannot be performed in a blinded way. Also, it is a pilot study done with the device to gather preliminary data**

1. Justification of why participants will not receive routine care or will have current therapy stopped.

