There are no penalties for completing the protocol except that the gift cards will have to be returned back.

1. **Costs**
2. Detail costs of study procedure(s) or drug (s) or substance(s) to participants and identify who will pay for them.

The study is being funded by a small grant received by the Thyroid Tumor Center (under the stewardship of [name]) that is a subsidiary of the Division of Endocrinology, Department of Medicine, Johns Hopkins Hospital.

|  |  | ***Run-***  ***Up-days***  ***0*** | ***Day 0***  ***9.00 am*** | ***Day 0***  ***3 pm*** | ***Day 1***  ***9 am*** | ***Follow up***  ***Day***  ***7*** |
| --- | --- | --- | --- | --- | --- | --- |
|  |  | ***-4 ± 1*** |  |  |  |  |
| ***Stop anti-thyroid meds*** | | ***X*** |  |  |  |  |
| ***I-123 dose*** | |  | ***X*** |  |  |  |
| ***COTI measurement*** | |  | ***X0*** | ***X0*** | ***X0*** |  |
| ***Uptake Measurement by probe (SOC)*** | |  | ***X*** | ***X*** | ***X*** |  |
| ***I-123 Planar scan*** | |  |  | ***X*** |  |  |
| ***Informed Consent*** | |  | ***X0*** |  |  |  |
| ***Review Eligibility*** | |  | ***X0*** |  |  |  |
| ***Medical History*** | |  | ***X*** |  |  |  |
| ***Physical Exam*** | |  | ***X*** |  |  |  |
| ***Vital Signs*** | |  | ***X*** |  |  |  |
| ***Clinical Labs*** | |  | ***X*** |  |  |  |
| ***Pregnancy Test-eligible*** | |  | ***X*** |  |  |  |
| ***Place Collar*** | |  | ***X0*** |  |  |  |
| ***Give instructions*** | |  | ***X0*** |  |  |  |
| ***Questionnaires*** | |  | ***X0*** |  |  |  |
| ***Adverse Events*** | |  | ***X0*** |  |  |  |
| ***Concomitant***  ***Medications*** | |  | ***X0*** |  |  |  |

***Table A Schedule of Visits after 123 dose for Graves disease Patients – All the visits marked with superscript (o)are part of research-Imaging schedule after I-123 dose***

|  | ***Visit***  ***No.*** | ***Run-***  ***up***  ***0*** | ***Day***  ***0***  ***9 am*** | ***Day***  ***1***  ***9 am*** | ***2***  ***9***  ***am*** | ***3***  ***9***  ***am*** | ***4***  ***9***  ***am*** | ***5*** | ***6*** | ***Follow-***  ***up***  ***7***  ***9am*** |
| --- | --- | --- | --- | --- | --- | --- | --- | --- | --- | --- |
| ***Activity*** | ***Days*** | ***-4 ± 1*** | ***0*** | ***1*** | ***2*** | ***3*** | ***4*** | ***5*** | ***6*** |  |
| ***Stop thionamide***  ***anti-thyroid meds*** | | ***X**** |  |  |  |  |  |  |  |  |
| ***I-131 200 µ administration*** | |  | ***X**** |  |  |  |  |  |  |  |

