| ***Uptake Measurement*** | |  | ***X**** | ***X**** |  |  |  |  |  |  |
| ***Informed Consent*** | |  | ***X**** |  |  |  |  |  |  |  |
| ***Review Eligibility*** | |  | ***X**** |  |  |  |  |  |  |  |
| ***Medical History*** | |  | ***X**** |  |  |  |  |  |  |  |
| ***Physical Exam*** | |  | ***X**** |  |  |  |  |  |  |  |
| ***Vital Signs*** | |  | ***X**** |  |  |  |  |  |  |  |
| ***Clinical Labs*** | |  | ***X**** |  |  |  |  |  |  |  |
| ***Pregnancy Test*** | |  | ***X**** |  |  |  |  |  |  |  |
| ***Place Collar*** | |  | ***X**** |  |  |  |  |  |  |  |
| ***Give instructions*** | |  | ***X**** |  |  |  |  |  |  |  |
| ***Questionnaires*** | |  | ***X**** | ***X**** |  |  |  |  |  |  |
| ***SPECT $*** | |  | ***X* 3pm*** | ***X**** | ***X**** | ***X**** |  |  |  |  |
| ***COTI measurement$*** | |  | ***X* 3pm*** | ***X**** | ***X**** | ***X**** | ***X**** |  |  |  |
| ***Low dose CT for attenuation correction*** | |  |  | ***X**** |  |  |  |  |  |  |
| ***Adverse Events*** | |  | ***X**** | ***X**** |  |  |  |  |  |  |
| ***Medications*** | |  | ***X**** | ***X**** |  |  |  |  |  |  |

***Table B- Imaging schedule for Graves disease low dose I-131 scan, COTI measurement and SPECT CT at 3 pm that day-The schedule marked with superscript are part of the research.This is a research scan.***

| ***SCHEDULE OF PROCEDURES*** | | | | | | | | | | | |
| --- | --- | --- | --- | --- | --- | --- | --- | --- | --- | --- | --- |
|  | ***Visit***  ***No.*** | ***Run-***  ***up***  ***0*** | ***Day***  ***1***  ***Time***  ***9.00 am*** | ***2***  ***9***  ***am*** | ***3***  ***9 am*** | ***4***  ***9 am*** | ***5***  ***9***  ***am*** | ***6*** | ***7*** | ***8*** | ***Day***  ***11*** |
| ***Activity*** | ***Days*** | ***-4 ± 1*** | ***0*** | ***1*** | ***2*** | ***3*** | ***4*** | ***5*** | ***6*** | ***7*** |  |
| ***Low iodine diet*** | | ***-14 +/-1 day*** |  |  |  |  |  |  |  |  |  |
| ***Informed Consent*** | |  | ***X*** |  |  |  |  |  |  |  |  |
| ***Review Eligibility*** | |  | ***X1*** |  |  | ***X1*** |  |  |  |  |  |
| ***Medical History*** | |  | ***X1*** |  |  |  |  |  |  |  |  |
| ***Physical Exam*** | |  | ***X1*** |  |  |  |  |  |  |  |  |
| ***Vital Signs*** | |  | ***X1*** |  |  | ***X1*** |  |  |  |  |  |
| ***Clinical Labs*** | |  | ***X1*** |  |  |  |  |  |  |  |  |
| ***Pregnancy Test*** | |  |  | ***X1*** |  |  |  |  |  |  |  |
| ***Thyrogen Injection*** | |  | ***X1*** | ***X1*** |  |  |  |  |  |  |  |

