| ***Diagnostic I-123 dose (1 pm)*** | |  |  | ***X1*** |  |  |  |  |  |  |  |
| ***Diagnostic WBS (11 am)*** | |  |  |  | ***X1*** |  |  |  |  |  |  |
| ***I-131 30 mci (1PM)*** | |  |  |  |  | ***X1*** |  |  |  |  |  |
| ***Give instructions*** | |  | ***X1*** |  |  |  |  |  |  |  |  |
| ***Questionnaires*** | |  | ***X1*** |  |  |  |  |  |  |  |  |
| ***COTI placement*** | |  |  |  |  | ***X*** |  |  |  |  |  |
| ***COTI measurement*** | |  |  |  |  | ***X*** | ***X*** | ***X*** | ***X*** | ***X*** | ***X*** |
| ***SPECT*** | |  |  |  |  |  | ***X*** | ***X*** | ***X*** |  | ***X1*** |
| ***Low dose CT for attenuation*** | |  |  |  |  |  | ***X*** |  | ***X*** |  | ***X1*** |
| ***Review of Risks***  ***Benefits*** | |  | ***X*** |  |  |  |  |  |  |  |  |
| ***Adverse Events*** | |  | ***X1*** | ***X1*** |  | ***X1*** |  |  |  |  |  |
| ***Concomitant***  ***Medications*** | |  | ***X1*** | ***X1*** |  | ***X1*** |  |  |  |  |  |

***Table C -Thyroid Cancer Patients-The events not marked with a superscript 1 are part of research. The events in red are part of research protocol. Imaging and visit schedule for thyroid cancer***

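### No schedule has a questionnaire at the end of collar use, and in thyroid cancer patients the only one precedes placement by three days, so Aim 3 (Abstract) is largely unserved

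*Protocol*

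**What the plan says.** The Abstract of the protocol lists three aims. The third is to "Evaluate patient experience, convenience, and discomfort in using the CoTI device with a survey instrument". It is not repeated among the primary or secondary objectives, and the Study Statistics section does not mention a survey.

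The procedures text mentions a questionnaire once, under Data collection, follow up, in the list of baseline data: "quality of life scores as measured by a questionnaire". No survey of the device is named there.

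Each of the three schedules at the end of the protocol has a row labelled only as questionnaires:

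- **Table A** (Group I(A)): one entry, Day 0 at 9 am, in the same column as collar placement. It carries the research mark.
- **Table B** (Group I(B)): entries on Day 0 and Day 1, both with the research mark. The collar is placed on Day 0.
- **Table C** (Group II): one entry, "Questionnaires* | | | *X1", which falls in the Day 1 column. The placement row, "COTI placement* | | | | | | *X", falls in the Day 4 column. The superscript 1 on the questionnaire entry marks it as not part of the research, according to the table's own key.

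**The concern.** Patients can report on using a device only after they have used it. A questionnaire given before placement, or at the placement visit, can record expectations or general quality of life, but not how the collar was tolerated over the days that followed.

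The protocol expects problems that may develop with wear. Its Risks section names pressure, skin irritation, rubbing over a recent surgical scar and discomfort on swallowing. The patients with recent neck surgery are in Group II, which is the group with no questionnaire after placement.

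Visit timing is fixed in the protocol's schedule. If answers are not collected when the collar comes off, no later analysis plan can recover them. With five patients per group, each missing answer is 20% of the group (1/5).

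**Working it through.** No sample-size or power calculation applies. The check sets the questionnaire column against the placement column and the last CoTI reading in each table.

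| | Table A, Group I(A) | Table B, Group I(B) | Table C, Group II |
|---|---|---|---|
| Questionnaire | Day 0, 9 am | Day 0 and Day 1 | Day 1 |
| Collar placed | Day 0, 9 am | Day 0 | Day 4 |
| Last CoTI reading | Day 1, 9 am (24 h) | Day 4 (96 h) | Day 11 (day 7 after I-131) |
| Last questionnaire relative to placement | 0 h (same visit) | about +24 h | 1 − 4 = −3 days |
| Reading window after last questionnaire | 24 − 0 = 24 h | 96 − 24 = 72 h | all 11 − 4 = 7 days |

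**Table C.** The questionnaire precedes the last reading by 11 − 1 = 10 days. The table's second header row counts days from 0, but the three-day gap between questionnaire and placement is the same on either count.

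**Table B.** The last questionnaire comes at 24/96 = 25% of the reading window.

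**Are the columns reliable?** The tables were read from PDF, so I compared other rows with the text. In Table C, recombinant TSH on Days 1 and 2, I-123 on Day 2, the whole-body scan on Day 3 and I-131 on Day 4 match the Group II preparation section. The readings at 0, 6 and 24 h in Table A, and the readings to 96 h in Table B, match the Scheduled Imaging times section. A shifted column does not explain the finding.

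**Does another row fill the gap?** The follow-up Day 7 column in Tables A and B has no entries. The adverse-event rows stop at Day 0 in Table A, Day 1 in Table B and Day 4 in Table C. In each table that is before, or at most 24 h into, the reading period.

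**Which form is the questionnaire row?** There are two possibilities:

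1. It is the Aim 3 survey. It is then mistimed in Tables A and C, and early in Table B.
2. It is the baseline quality-of-life form. Its timing is then sensible, and the Aim 3 survey has no scheduled time in any table.

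The protocol does not settle this. The baseline wording in the text and the non-research mark in Table C favour the second. The research marks in Tables A and B, and the repeat on Day 1 of Table B, leave the first open. On either reading, no table has a survey at the end of the reading period.

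**The case against.** A reader might infer that every questionnaire falls before or at placement and that Aim 3 therefore cannot be answered at all. The documents do not support that. Table B has a questionnaire on Day 1, about 24 h after placement, so some early experience could be collected in Graves patients if that form asks about the device.

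A reader might also count Group I(A) as contributing nothing. That assumes separate patients. The protocol plans five patients per group and ten in all, treats A and B as parts of Group I, and names I-123 together with low-dose I-131 in the Graves objective. The same five patients may well follow both tables. Their Table B Day 1 questionnaire would then follow wear, and the Table B Day 0 one might follow the Table A wear. The interval between the two tables is not stated.

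Three further points have weight:

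- The 25% is a share of the reading window, not of wear. No removal time is given, and patients may take the collar off for some hours each day or at any time.
- Discomfort is not wholly unobserved. Patients have a contact to call, tolerability is among the stopping rules, and the investigator monitors safety. None of these is a survey of all patients, so they do not meet the aim.
- Aim 3 appears only in the Abstract. The radioiodine comparison does not depend on it. The Abstract links a possible larger study to Aim 2, so it should not be claimed that this gap undermines that study's planning.

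These points limit the reach and severity of the concern. They do not supply a questionnaire after placement in Table C, or one at the end of the reading period in any table.

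**Conclusion.** The point stands, with moderate severity. Followed as written, the schedules give post-wear answers from none of the five Group II patients. In Graves patients the latest answer comes about 24 h into the 96 h Table B window. Whether that reaches all five depends on whether the same patients follow Tables A and B: if they do, at most 5 of 10 participants have any questionnaire after placement; if they do not, fewer than five do.

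This rests on reading the table cells as printed and on the last CoTI reading as a stand-in for the end of wear. It does not rest on the questionnaire row being the Aim 3 survey: if that row is a baseline quality-of-life form, the survey is missing from the schedule rather than mistimed.

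**What to change.** 1. Keep the current questionnaire entries and label them as baseline quality of life. State what the Day 1 entry in Table B is for.
2. Name the Aim 3 device-experience survey as a separate row, marked as research in all three tables.
3. Schedule it at the last CoTI reading: Table A Day 1, Table B Day 4, Table C Day 11.
4. Give it at permanent removal if that comes earlier. The protocol withdraws participants who cannot use the device for the planned time. A survey of completers only would leave out the patients who tolerated it least.
5. State that this post-wear survey is the Aim 3 outcome.

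The cost is three table edits and a few minutes at visits already scheduled for CoTI readings, with no added visit at those times. The change should be made before enrolment, because answers missed at removal cannot be collected reliably afterwards.

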## Primary Objective;

To perform a pilot (exploratory) study using a novel AG Medical Collar Therapy Indicator (CoTI) to evaluate the variability in radioiodine kinetics across patients treated for hyperthyroid Graves disease and postoperative thyroid remnant ablation for thyroid cancer.

- - For Graves disease, after administration of 0.2 mci I-123 and low dose (200 µCi) I-131, to compare conventional 6, 24, 48 and 72-hour fractional thyroidal radioiodine uptakes with single photon emission (with low-dose computed tomography [SPECT/CT] for quantification and attenuation correction) with the activity measured continuously by the COTI device, which is placed in collar around the neck resembling a turtle neck sweater collar with a wire and recording box.
  - For remnant ablation, after therapeutic administration of 30 mCi I-131, to compare conventional 24, 48, 72 hr. and 7-day SPECT (with low dose CT for quantification and attenuation correction performed at 24, 48, 72 hours and 7 days) with the activity continuously measured by the COTI device, as described above.

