**Scheduled Imaging times (Tables at the end);**

**Group I (A) - Persons with Graves disease**

After I-123 diagnostic dose;

- An uptake at 0 hours -for background at 9 am

- A planar image with a pinhole collimator at time 06.00 hours with an uptake at the same time.

- An uptake only measurement (with the probe) at time 24.00 hours.

- The counts from the handheld device connected to the CoTI would be obtained at similar times i.e. 0, 6 and 24 hours.The total duration of each visit would be an hour.

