**Group I (B) --Persons with Graves disease**

After administration of 200 µCi of I-131 dose;

- A first SPECT image would be performed at 6 hours after I-131 dose.

-A Second SPECT image (with a low dose CT for quantification and attenuation correction) would be performed at 24 hours after I-131 dose.

-A third SPECT image at 48 hours.

-A fourth SPECT image at 72 hours.

- The counts from the handheld device connected to the CoTI would be obtained at similar times as above with one additional time point of 96.00 hours i.e. 6, 24, 48, 72 and 96.

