**No non-FDA drugs will be administered. The CT scans are expected to be without iodinated contrast agents.**

Date: ____________________

Principal Investigator: _________________

Application Number: ___________

1. **Study Statistics**
2. Primary outcome variable.
3. Secondary outcome variables.
4. Statistical plan including sample size justification and interim data analysis.

This is a pilot study involving 10 patients and hence there are no interim data analysis or conflicts regarding sample size. Descriptive data will be outlined for all the participants tabulating the variables as determined. The intrapatient variability as well as accuracy and precision of the device will be obtained individually for Group I and Group II patients. The correlation (non-parametric) Spearman correlation coefficient will be obtained to assess the relationship between the uptake and findings as obtained by the collar device and conventional methods of uptake measurement.

1. Early stopping rules.

Early Stopping Rules Include but not limited to:

1. Severe, unexplained discomfort with the device. (2) Lack of device tolerability or interference with optimal functioning of daily activity (3) Discomfort after stopping anti-thyroid treatments causing rebound hyperthyrodism
2. **Risks**
3. Medical risks, listing all procedures, their major and minor risks and expected frequency. b Steps taken to minimize the risks.

The following risks are anticipated:

• Pressure sensation and possible skin irritation due to compression of skin around the neck. The patients can remove the collar for a few hours every day to avoid this.

• Transient redness around the neck if the collar is placed too tightly.

• For persons with prior thyroid surgery, the device might give cause an unpleasant rubbing sensation, especially if the surgical scar is very fresh.

• Rarely, it could cause patients to experience discomfort with swallowing, but the patients will be given all the necessary information to prevent this. If the participants feels uncomfortable, he/she can remove the device anytime

• The participants will also receive 1-4 low-dose CT scans. The cumulative radiation doses will be very low. Radiation imposed minimal risk at very low doses.

- The participants will undergo a low dose 0.2 mci I-131 dosing that is not associated with thyroid “stunning” and is much less than the 12 mCI (about 60 times 0.2) that they will receive for theraupetic treatment of graves disease

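### The Graves primary objective promises a 6 to 72 hour SPECT/CT comparison after both tracers, but after I-123 no SPECT is scheduled and nothing is measured beyond 24 hours; accuracy is set for Group I without separating the tracers

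*Protocol*

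**What the plan says.** The Graves bullet under Primary Objective opens "For Graves disease, after administration of 0.2 mci I-123 and low dose (200 µCi) I-131" and then sets one comparison for the collar: "to compare conventional 6, 24, 48 and 72-hour fractional thyroidal radioiodine uptakes with single photon emission" tomography, with low-dose CT for quantification and attenuation correction.

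The Scheduled Imaging times section and the schedule tables split Group I in two.

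- **Group I (A), I-123.** After a background uptake at 0 hours come "A planar image with a pinhole collimator at time 06.00 hours with an uptake at the same time" and "An uptake only measurement (with the probe) at time 24.00 hours". Collar counts "would be obtained at similar times i.e. 0, 6 and 24 hours". Table A agrees and names the probe as the uptake method on all three occasions. It has no SPECT or CT row, and its day 7 follow-up column is empty.
- **Group I (B), I-131.** "A first SPECT image would be performed at 6 hours after I-131 dose", and SPECT follows at 24, 48 and 72 hours. CT is attached to one of these: "A Second SPECT image (with a low dose CT for quantification and attenuation correction) would be performed at 24 hours after I-131 dose". Table B agrees. It also lists an uptake measurement on days 0 and 1 without naming the method; the Group I (B) imaging times do not mention it.

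The Study Statistics section says that intrapatient variability and the "accuracy and precision of the device will be obtained individually for Group I and Group II patients". The sentence on Spearman correlation names no group, tracer or time point.

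**The concern.** Anyone reading the objective alone would expect, for each tracer, collar data set against SPECT-based uptake out to 72 hours. The Abstract strengthens that expectation: its aims include comparing the collar with an imaging-derived time-activity curve and describing uptake and clearance kinetics. If the I-123 schedule cannot supply such a curve, part of the primary objective fails before any patient is enrolled, and no analysis plan can recover measurements that were never scheduled.

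The second issue is the level of reporting. Accuracy has meaning only against a stated reference. Group I has probe uptake after I-123 and SPECT after I-131, yet the statistics section names the group and not the tracer or the reference. One Group I figure would combine device error with differences between tracers and between reference methods, and would describe neither setting.

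**Working it through.** The plan gives no power calculation or other figure to reproduce on this point. The check sets the objective's time points against the two schedules.

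| Time in objective | I-123: SPECT | I-123: other reference | I-123: collar reading | I-131: SPECT | I-131: CT | I-131: collar reading |
|---|---|---|---|---|---|---|
| 6 h | no | uptake and planar image | yes | yes | no | yes |
| 24 h | no | uptake | yes | yes | yes | yes |
| 48 h | no | none | none | yes | no | yes |
| 72 h | no | none | none | yes | no | yes |

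(Sources: Primary Objective; Group I (A) and Group I (B) under Scheduled Imaging times; Tables A and B.)

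For I-123, SPECT covers 0 of 4 time points and any reference covers 2 of 4. For I-131, SPECT covers 4 of 4 and CT 1 of 4.

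**Number of pairs.** Study Procedures gives five patients per group. Assume that all five Graves patients receive both tracers, which the protocol does not state outright.

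- Collar/SPECT pairs implied by the objective: 5 patients × 2 tracers × 4 times = 40.
- Collar/SPECT pairs scheduled: 5 × 4 = 20, all after I-131, of which 5 × 1 = 5 have CT at the same time.
- Collar/uptake pairs after I-123 at the objective's times: 5 × 2 = 10.

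A single Group I set at these times would then hold 10 + 20 = 30 pairs, of which 10/30 = 33% come from I-123. If the five patients were instead divided, with *a* of them in I(A), the share is 2*a* / (2*a* + 4(5 − *a*)): 2/18 = 11% for *a* = 1 and 8/12 = 67% for *a* = 4. The size of the share is uncertain, but both tracers are present in every case.

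**What mixing could do (illustration only).** Spearman's coefficient was simulated for 10 pairs from one stratum and 20 from the other, with 4,000 replicates, normal data and pairs treated as independent. The shifts are assumed values; the documents give none.

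- No true correlation within either stratum, with both collar and reference shifted between strata by 1, 2 or 3 SD: the mean pooled coefficient is 0.18, 0.48 or 0.63 when the shifts have the same direction, and −0.18, −0.47 or −0.63 when they are opposite.
- Correlation of 0.9 within each stratum, with only the reference offset by 0, 1, 2 or 3 SD: the mean pooled coefficient is 0.87, 0.78, 0.61 or 0.51.

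A pooled coefficient could therefore suggest agreement that is absent or hide agreement that is present.

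**The case against.** **The objective can be read more loosely.** The bullet might mean conventional uptakes for I-123 and SPECT for I-131. That removes the conflict over the method, but not over the times: 48 and 72 hours still have neither a reference nor a scheduled collar reading after I-123. Nor does the collar's continuous recording help, since without a reference there is nothing to compare it with.

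**Pooling is not stated.** A reader might infer that the plan merges I(A) and I(B) into one accuracy figure. The text does not go that far. It asks for results by Group I and Group II, prescribes no single Group I number, and in the Spearman sentence refers to conventional methods in the plural. Elsewhere the protocol keeps I(A) and I(B) apart in preparation, imaging times and tables, and a statistical analysis plan that is not shown could separate them. This objection stands. What remains is that the one level of reporting the protocol fixes is coarser than its own design.

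**The references may be meant to share a scale.** The objective speaks of fractional uptakes with SPECT, so it would be wrong to say that one method yields percent uptake and the other does not. They are still different methods. A reader might add that the collar responds differently to the two tracers; the documents give no figure on that, and nothing here rests on it.

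**The secondary objective does not demand separation.** It names the two Graves tracers jointly, so it cannot be cited as requiring separate results.

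**This is a small descriptive pilot.** Ten patients are planned, and collar readings do not guide treatment. That limits the consequences, but a pilot's primary objective should still be one that its schedule can meet.

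**Conclusion.** The mismatch holds. After I-123 the schedule supplies SPECT at 0 of the 4 time points in the primary objective and any reference at 2 of 4, so that part of the objective cannot be met as written on either reading. After I-131 the SPECT times match, but CT is scheduled at 24 hours only. These counts need no assumption beyond the schedules.

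The reporting point holds in a weaker form. The protocol sets accuracy and precision by Group I and Group II although Group I contains two tracers with different reference methods. It says neither that they are combined nor that they are kept apart. The harm from mixing is conditional on a single Group I figure being produced; the 33% share assumes that all five Graves patients receive both tracers, and the simulated coefficients rest on assumed shifts.

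This should be corrected before the results are interpreted. It is an internal inconsistency in the primary objective and does not make the study unworkable.

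**What to change.** Reconcile the Graves bullet of the Primary Objective with the Group I (A) and I (B) imaging times and Tables A and B by stating two comparisons:

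- I-123, Group I (A): collar against uptake measurement at 6 and 24 hours.
- I-131, Group I (B): collar against SPECT at 6, 24, 48 and 72 hours, noting that low-dose CT is scheduled at 24 hours only.

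In Study Statistics, replace reporting by Group I and Group II with reporting of variability, accuracy, precision and Spearman correlation separately for I(A), I(B) and II, naming the reference method for each. The I(B) entry should also say what role, if any, the uptake measurements listed in Table B on days 0 and 1 play.

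This changes wording only and adds no visit, scan or procedure. The price is that the I-123 claim is limited to 24 hours, and statements about Graves clearance kinetics beyond 24 hours rest on I-131 alone, which is all that the present schedule supports.
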